### Study design

We propose a phase II, multicentre Bayesian trial. A total of 155 patients will be randomized in a 1:3 ratio to CL-RT (39 patients) or VC-RT (116 patients). Patients will be stratified by tumor stage (T1a/T1b) and by site (Fig. 1). This study, which is registered on clinicaltrials.gov (NCT03759431), will include tertiary, academic hospitals in Canada and the United States. One dose and fractionation regimen will be determined by each participating center and will have to be the same in both arms. The study is powered to compare LC of VC-RT compared to historical outcomes of CL-RT. The purpose of the randomization will be to generate data on secondary outcomes of voice impairment, dysphagia and quality of life as well as survival outcomes in the control arm.

**Fig. 1 Fig1:**
[figure not shown]
Study Scheme of the VOCAL Trial. N = Number of patients

### Conditions for patient eligibility

Age > 18 yearsStage T1a-b N0 of the true vocal cords planned for definitive RTPatient not candidate for laser surgery or declined laser surgeryBiopsy-confirmed squamous cell carcinoma, including verrucous carcinomaEastern Cooperative Oncology Group (ECOG) performance status 0–2Ability to provide written informed consent.Ability to understand and read English or French at a level adequate for completion of patient reported outcomes questionnaires

### Conditions for patient ineligibility

Previous irradiation of the head and neck regionPregnancy or breastfeedingAny medical condition that represents, in the opinion of the investigator, a contraindication to radiotherapy or would prevent follow-up after radiotherapy.Prior invasive malignancy (except non-melanomatous skin cancer) unless disease free for a minimum of 2 years.

### Required pre-treatment evaluation

History and Physical Examination, including:
° Laryngoscopy, with detailed diagram of the primary lesion confirmed by both the radiation oncologist and head and neck surgeon° Biopsy of the primary tumorPatient reported outcomes questionnaires including the Voice Handicap Index 10 (VHI-10), the MD Anderson Dysphagia Inventory (MDADI) and the MD Anderson Symptom Inventory Head and Neck Module (MDASI-HN).

### Intervention

In both treatment arms, patients will be treated with a radical course of radiotherapy using a standard mild hypofractionation regimen of 5 fractions per week, over 4 to 6 weeks. For pragmatic reasons, each participating institution is allowed to use their standard of care dose and fractionation, but will have to be identical between the standard and experimental arms at each institution. Each center will provide, at time study entrance, what dose and fractionation will be used. This dose and fractionation will be the same for both arms and cannot change over the course of the study. The study is stratified by participating institution, which means that it will be stratified by dose/fractionation. In both treatment arms, a daily volumetric imaging method will be required for set-up verification, with match on the larynx.

#### Immobilization and simulation

Patients will be positioned in a comfortable and reproducible position and will be immobilized in a thermoplastic mask of the head and shoulders fixed to the treatment Table. A 3-dimensional planning computed tomography (CT) scan (maximum slice thickness of 1.5 mm) of the neck will be obtained. A planning magnetic resonance imaging (MRI), co-registered to the planning CT to help define gross tumor volume (GTV), is recommended but optional.

Clinicians should be aware of the risk of swallowing during CT simulation. Patients should be instructed not to swallow during the planning CT and MRI, as well as during their radiation treatment. Co-registration of the planning CT with a complementary planning volumetric imaging (such as MRI or contrast-enhanced CT) should be performed in order to verify the position of the larynx. If only one simulation imaging is obtained at time of planning, the position of the larynx should be verified on the first fraction of radiotherapy using a volumetric imaging method allowing 3D image reconstruction (Ex: Cone beam CT, CT on rail, MR-Linac).

#### Volumes

The GTV will be the same for both CL-RT and VC-RT and will be based physical examination and imaging (planning CT +/− MRI).

##### Standard arm (CL-RT)

The RT volume in the standard arm is based on expected fields from conventional CL-RT volume, with the planning target volume (PTV) extending from the top of thyroid cartilage lamina superiorly, to the bottom of the cricoid inferiorly. The volumes below are defined to lead to traditional volumes from conventional CL-RT (Fig. 2).
CTV_CL-RT_ = GTV plus a manual expansion superiorly to include the cranial arytenoid cartilage, inferiorly to include 1–1.5 cm below true vocal cords, anteriorly to include the anterior commissure, posteriorly to include posterior commissure and arytenoid cartilage.PTV _CL-RT_ = 1 cm circumferential expansion around CTV _CL-RT_ in all directions, except posteriorly where the margin will be 0.5 cm. As the PTV of CL-RT is based on previous fields of conventional RT, after the addition of a 1 cm margin, the PTV _CL-RT_ should extend to the top of the thyroid cartilage lamina superiorly and to the bottom of the cricoid inferiorly; alternatively, the PTV _CL-RT_ should be manually expanded.

**Fig. 2 Fig2:**
[figure not shown]
Examples of VC-RT volumes in axial and sagittal view showing for a patient with right T1a glottic cancer (LEFT) and for a patient with T1b glottis cancer (RIGHT). The entire involved vocal cord (in T1a) or both vocal cords (in T1b) form the CTV (red); the ITV formed by an isotropic margin of 6 mm around the CTV (yellow) and the PTV is formed by additional 2 mm margin (green)

##### Experimental arm (VC-RT)

The RT volume would include the entire ipsilateral vocal cord in stage T1a disease, or both vocal cords in T1b disease. An internal target volume (ITV) consisting in an isotropic 6 mm margin will be added to account for respiratory motion. An additional margin of 2–3 mm margin will be added for setup uncertainty (Fig. 2).
CTV_VC-RT_ = GTV plus a manual expansion to include the entire ipsilateral vocal cord in stage T1a disease, or both vocal cords in stage T1b disease. In cases where the GTV is not visualized, only a CTV (comprising the entire involved vocal cord in T1a or both vocal cords in T1b) will be contoured.An internal target volume (ITV) will be added and will consist in an isotropic margin of 6 mm around the CTV_VC-RT_ to account for respiratory motion.PTV _VC-RT_ = ITV plus a 2–3 mm margin. This is smaller than in Arm 1, because internal motion is already accounted for in the ITV.

#### Dosimetry

Use of either IMRT or protons (passive scattering or intensity modulated proton therapy) will be mandatory for all plans. Treatment plans will be normalised so that 95% of the PTV volume be covered with the prescription dose. The maximal dose to the PTV cannot exceed 110% of the prescribed dose and the dose to 99% of PTV should be above 95% of the prescribed dose (D99 > 95% of prescribed dose). Heterogeneity correction will be required for dose calculation.

#### Critical structures delineation and constraints

Critical structures delineation will be based on previously published international consensus guidelines [61]. The latter reference provides a detailed atlas of each structure and should be consulted for additional precisions. Anatomic boundaries are details in *Supplementary material *1.

##### Standard arm (CL-RT)

Spinal cord: Not more than 0.03 cc of the planning organ at risk (PRV) exceeds 42 Gy and not more than 0.03 cc of the spinal cord receives > 40 Gy.Optimization of dose to other organs at risk (OAR) is not required. However, carotid-sparing is authorized.

##### Experimental arm (VC-RT)

Spinal cord: Not more than 0.03 cc of the PRV exceeds 42 Gy and not more than 0.03 cc of the spinal cord receives > 40 Gy.Additional dose specification goals that should not take priority over PTV coverage:
° Carotid arteries:
▪ T1aIpsilateral carotid: Mean dose < 35 GyControlateral carotid: Mean dose < 15 Gy▪ T1b
Mean dose to carotids < 35 Gy° Supraglottic larynx: Mean dose < 45 Gy° Contralateral vocal cord: Mean dose < 50 GyDoses to other organs should be minimized and documented.

#### IGRT

A volumetric imaging method allowing 3D image reconstruction (Ex: Cone beam CT, CT on rail, MR-Linac) will be required daily for set-up verification. Additional images (e.g. confirmatory kV X-ray) may be used as supplemental verification. Larynx soft-tissue matching is required (as opposed to bony landmark [e.g. spine, base of skull] alignment).

### Study assessments

There will be evaluation immediately post-treatment, as well as at 6, 12 and 24 months post-treatment as part of the study. Other follow-ups will be as per institution standard of care, but suggested schedule of assessments detailed in Table 1 is encouraged.Alternate follow-ups between the head and neck surgeon and the radiation oncologist will be mandatory.Physical examination will involve flexible laryngoscopy or/and videostrobe or/and mirror examination with adequate visualisation of vocal cords.Clinical follow-up will involve documentation of LC and survival status as well as reporting of CTCAE V4.03 toxicities.Patients will be asked to fill patient-reported outcome questionnaires at baseline and at each visit, as detailed in Table 1. The questionnaires will be administered in the following order: VHI-10, MDADI and MDASI-HN. The questionnaires could be filled in paper format, or online using the anonymized CASTOR EDC system. The questionnaires will not be reviewed during the study and will be analysed only at the pre-specified timepoints.There will be an *optional* assessment of acoustic and objective measures of voice analysis by a speech pathologist at baseline, immediately post-treatment and at 6 months post treatment. The assessments will consist in a digital recording of a standard oral reading passage and a short monologue, which would later be analyzed for specific acoustic variables and microacoustic measures of the cycle-to-cycle variation of acoustic parameters (in frequency and intensity domains). The voice quality will be graded as per then GRBAS scale (grade, roughness, breathiness, asthenia, strain).

**Table 1 Tab1:** Suggested Schedule of Assessments

	Pre-RT	End of RT	2mo^a^	6mo	12 mo	24 mo	36mo^a^	48mo^a^	60mo^a^
History (including TIA or stroke) & physical exam (including laryngoscopy)	x	x	x	x	x	x	x	x	x
Side effects			x	x	x	x	x	x	x
TSH^a^	x				x	x	x	x	x
Questionnaire VHI −10	x	x	x	x	x	x	x	x	x
Questionnaire MDADI and MDASI-HN	x	x	x	x	x	x	x	x	x

*RT* Radiotherapy, *Mo* months

^a^Optional assessments

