## Methods/design

### Study objectives

The objective of this trial is to assess the efficacy and safety of VC-RT, compared to CL-RT, in T1N0 glottic squamous cell carcinoma.

Primary endpoint:
Local control at 2-year after the end of RT.

*Local control will be defined as absence of biopsy proven recurrence within the larynx.*

Secondary endpoints:
Patient-reported outcomes including dysphagia, voice impairment, and symptom burden.Acute and late toxicity radiation-induced toxicityOS and progression free survival (PFS)Acoustic and objective measures of voice analysis using the Consensus Auditory-Perceptual Evaluation of Voice.

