### Analytic plan

A Bayesian regression model [63, 64] will be used to compare the LC between the VC-RT and CL-RT arms at 2 years. The LC and OS time will be defined from end of RT date. The following recurrences will be considered LC: in field, field margin and within larynx. Local recurrences will be biopsy-proven when possible. Competing events will include local recurrence, regional/distant recurrence and death prior to recurrence. LC will be estimated using both competing risk and Kaplan -Meier (KM) analysis. The analyses will be conducted using SAS and R software. A Cox multivariable regression analysis will be used to determine factors predictive of LC, PFS and OS. Chi-squared test or Fisher’s exact test will be used to compare the difference in toxicity between arms. For the secondary endpoints of patient-reported outcomes (VHI-10, MDADI and MDASI-HN), trajectory trends of scores between/among arms over time will be explored using a generalized linear mixed model with a random effect of time. Appropriate adjustments for covariates will be considered.

There will be two planned analysis: 1) an interim analysis and, 2) a final analysis. The interim analysis will be done after 55 patients on the experimental arm have a minimum follow-up of 6 months. A short follow-up time of 6 months was chosen for the interim analysis for safety (i.e. for early detection of local recurrence trends). The trial may be interrupted early if VC-RT is deemed not promising on interim analysis. The final analysis will performed 2 years after accrual is completed.

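### The 2-year landmark falls on the 24-month visit, with no event-date rule and two different biopsy requirements, so recurrences found at that visit could count as local control

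*Protocol article*

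**What the plan says.** All references are to the protocol article.

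- **Endpoint (Study objectives).** The primary endpoint is "Local control at 2-year after the end of RT". The definition attached to it is "Local control will be defined as absence of biopsy proven recurrence within the larynx".
- **Event and time (Analytic plan).** The time origin is fixed: "The LC and OS time will be defined from end of RT date". The biopsy requirement is softer here: "Local recurrences will be biopsy-proven when possible". On estimation: "LC will be estimated using both competing risk and Kaplan -Meier (KM) analysis".
- **Visits (Study assessments).** "There will be evaluation immediately post-treatment, as well as at 6, 12 and 24 months post-treatment as part of the study". For the remainder: "Other follow-ups will be as per institution standard of care, but suggested schedule of assessments detailed in Table 1 is encouraged". Table 1 has no column between 12 and 24 months. The same section makes alternating follow-up by surgeon and radiation oncologist mandatory, without giving its frequency.
- **Data cut (Analytic plan).** "The final analysis will performed 2 years after accrual is completed".
- **Decision rule (Statistical considerations).** VC-RT is acceptable if 2-year LC is at least 84%, against an expected 92%. The test is a one-sided exact binomial test at 0.05 with 111 patients, and the stated power is over 82%.

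The article does not say which date ends LC time (first suspicion, examination or biopsy), and gives no window around the 24-month visit.

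**The concern.** When the landmark and the detecting visit fall on the same day, the dating convention decides whether a recurrence found at that visit is a 2-year failure. Biopsy normally follows the examination that prompts it. Read literally, the definition in Study objectives means that a lesion seen at month 24 and biopsied afterwards was not a proven recurrence at 2 years. A visit held a little late has the same effect even if the examination date is used. The softer wording in Analytic plan allows the opposite classification, so two analysts could count the same patient differently.

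The possible error runs one way. It can only remove failures from the 2-year count, and the powered decision compares the VC-RT arm with a fixed 84%, so the same calendar in the CL-RT arm does not offset it. The data cut adds to the problem. LC time starts after a 4 to 6 week course, so patients accrued last cannot have reached 24 months when the final analysis falls 2 years after accrual ends. That leaves no time for a biopsy prompted by their last visit.

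**Working it through.** **Inputs.** From Statistical considerations: n = 111, unacceptable LC 0.84 (failure 0.16), target LC 0.92 (failure 0.08), one-sided exact binomial test at 0.05. The share *s* of true 2-year failures dated after 24 months is an assumption; the article gives no figure for it.

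**Step 1: reproduce the plan's figure.** With X the number of failures, the largest *c* with P(X ≤ c | 111, 0.16) ≤ 0.05 is 11:

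- P(X ≤ 11 | 0.16) = 0.0464 and P(X ≤ 12 | 0.16) = 0.0818, so the rule is at most 11 failures.
- Power is P(X ≤ 11 | 0.08) = 0.823, which agrees with the stated figure of over 82%.

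With 12 true failures, dating one of them late turns rejection into acceptance.

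**Step 2: late dating at a true LC of 84%.** Expected failures are 111 × 0.16 = 17.8. If a share *s* is dated late, the apparent failure rate is 0.16 × (1 − s), and false acceptance is P(X ≤ 11) at that rate.

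| s | Apparent failure | Patients dated late (17.76 × s) | False acceptance |
|---|---|---|---|
| 0 | 0.160 | 0 | 0.046 |
| 5% | 0.152 | 0.9 | 0.072 |
| 10% | 0.144 | 1.8 | 0.109 |
| 20% | 0.128 | 3.6 | 0.225 |

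Under the alternative, late dating makes power look better: at s = 10% the apparent failure rate is 0.072 and the chance of acceptance is 0.897.

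**Step 3: the ceiling.** Under an assumed constant hazard with 2-year LC of 84%, 48% of 2-year failures arise in months 12 to 24. If none of them were found before the 24-month visit and all were dated after the cut, false acceptance would lie between 0.62 (s = 40%) and 0.82 (s = 50%). That bounds the problem; it does not forecast it.

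**Step 4: would a later reading time cure it?** Suppose the primary estimate were read at 27 months and failures arose evenly over time. The target failure rate becomes 0.08 × 27/24 = 0.09, and power falls to P(X ≤ 11 | 0.09) = 0.70. Failures that arise after 2 years would then be charged against a threshold set for 2 years.

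**The case against.** A reader might infer that recurrences found at the 24-month visit are in fact dated after 2 years and counted as controlled. The article does not say so. It fixes the time origin and leaves the event date open, and its Analytic plan does not make biopsy a strict condition. Dating rules and visit windows are commonly left to a full protocol or SAP, neither of which is shown. This stands, so the point has to be conditional.

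A reader might also infer a true 12-month gap in examinations and quote a type I error near 82%. That does not hold either. The gap concerns study-required visits; standard-of-care and alternating specialist visits may fall within it. Figures built on the full gap are ceilings.

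The calculation uses the binomial test, whereas late dating is most obvious in a Kaplan-Meier or competing-risk estimate. The binomial test still needs each patient classified at 2 years, so the same convention decides. It is used here because it is the plan's own powered rule; inflation for the other estimators was not computed.

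How the historical series behind the 92% dated recurrences is unknown, and they may share some of the delay. The planned between-arm regression also has a common schedule. Both limit what can be said about bias relative to history or between arms. Neither removes the effect on a true 2-year LC judged against a fixed 84%. Follow-up to 5 years means that late confirmations can be recovered, but only if a rule assigns them to the 24-month assessment.

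What survives does not depend on a missing SAP rule alone. The article itself sets the landmark, the calendar, the data cut and two differing biopsy requirements.

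**Conclusion.** The point holds in conditional form. If recurrences are dated by biopsy, or by a visit held slightly late, and LC is read at exactly 24 months, recurrences found at the 24-month visit drop out of the 2-year failure count, always in favour of VC-RT. Because one patient can change the decision, a small late share matters: 5%, less than one patient among about 18 expected failures, moves false acceptance from 0.046 to 0.072, and 10% moves it to 0.109. The size rests on an assumed late share and on the exact test at n = 111. If events are assigned to the examination that found them, within a stated window, the late share is zero and the design keeps its alpha of 0.046 and power of 0.823. The change is worth making because it settles who counts as a primary-endpoint failure at almost no cost.

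**What to change.** 1. Reconcile Study objectives and Analytic plan on whether biopsy proof is required, and say how a recurrence that cannot be biopsied is classified.
2. Define a 2-year failure as any recurrence first suspected at or before the 24-month assessment and later confirmed, with a stated visit window. Date it at the examination that raised suspicion. Apply the same classification in the binomial test and in the Kaplan-Meier and competing-risk estimates, so that a visit late within the window is not lost at a cut of exactly 24 months.
3. Place the final data cut after the last patient's 24-month window and any biopsy that results from it.
4. Keep the primary estimate at 2 years and do not move it to 27 months, for the reason shown in step 4 of the working. An interval-censored estimate, using the date of the last recurrence-free laryngoscopy, is an optional sensitivity analysis.

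The cost is endpoint wording, one date field and a slightly later data cut, with no added visits. Slightly more failures will be counted. A visit late in its window may pick up a recurrence that arose just after month 24, so the window should be short.

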### Statistical considerations

According to previous experience, expected LC after CL-RT is estimated to be 92% [6, 8]. Assuming a non-inferiority margin of 8%, if LC in the VC-RT arm is ≥84% at 2-years, we will deem the VC-RT arm acceptable. With a sample size of 111 patients, over 82% power will detect a margin difference of 8%, at a target significance level of 0.05 using a one-sided, exact binomial test (NCSS-PASS 2005). The purpose of the randomization will be to generate currently unavailable data on secondary outcomes of voice impairment, dysphagia and quality of life in the CL-RT arm. Considering a 5% attrition rate, 155 patients will be randomized in a 1:3 ratio to CL-RT (39 patients) and VC-RT (116 patients) arms. Patients will be stratified by stage (T1a/T1b) and by institution.

An interim analysis will be conducted when 55 patients have a minimal follow-up of 6 months. We will monitor the efficacy endpoint using the Bayesian optimal phase 2 (BOP2) design [62]. Specifically, let *n* denote the interim sample size and *N* denote the maximum sample size. Let *p*_*eff*_ denote the probability of efficacy (response rate) and define the null hypothesis *H*_0_ : *p*_*eff*_ < 0.84, representing that the treatment is inefficacious. We will stop enrolling patients and claim that the treatment is not promising if
$$ \mathit{\Pr}\left({p}_{eff}\ge 0.84\mid data\right)<\lambda {\left(\frac{n}{N}\right)}^{\alpha }, $$where *λ* =0.95 and *α* =1 are design parameters optimized to minimize the chance of incorrectly claiming that an efficacious treatment is not promising (i.e., type II error) under the alternative hypothesis *H*_1_ : *p*_*eff*_ = 0.92, while controlling the type I error rate at 0.05 (i.e., the chance of incorrectly claiming that an inefficacious treatment is promising is no more than 5%). Assuming a Beta (0.84,0.16) prior distribution for *p*_*eff*_, if more than 10 patients among the 55 patients develop recurrences, the trial will be stopped in the interim analysis. Otherwise, the trial will be continued.

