The current phase II multicenter Bayesian trial will accrue 155 patients with T1N0 glottic cancer, randomized to VC-RT versus CL-RT. The study is limited by the fact that it does not constitute a true randomized non-inferiority trial, but the feasibility of such a design is rendered impossible by the unrealistic necessary sample size of > 2000 patients. Therefore, this trial would likely provide the best possible comparison between the 2 treatment arms. Local control at 2 years has been selected as the primary endpoint as the majority of local recurrences occur within the first 2 years after radiotherapy [66, 67], however, LC will continue to be monitored in the context of this trial up to 5 years after radiotherapy. LC in the literature for T1N0 of the glottic larynx varies between 85 and 95% [6–8, 24, 25].; this variation is at least partly dependent on the distribution of T1a versus T1b in the cohorts. With a target LC of 92% and a margin of 8%, any LC below 84% - therefore below the expected range- would be deemed unacceptable. In the context of this pragmatic trial, each center will use their own standard of care dose and fractionation regimen; as a general principle, radiotherapy will consist in mild hypofractionation regimen of 5 fractions per week, over 4 to 6 weeks. Institutions will not be allowed to change their dose/fractionation once accrual has started. As the study is stratified by participating institution, there will be a balanced number of patients with each dose/fractionation in each arm. In addition, as intensity modulated proton beam therapy is the standard of care for early glottic larynx cancer in some centers, the trial allows the use of proton beam therapy, as long as the same treatment technique is used in each arm.

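### The written acceptance rule uses 84%, the null value of the powered test, as its threshold, and the final analysis names a between-arm comparison for which the trial is not sized

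*Protocol article*

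**What the plan says.** Statistical considerations takes 92% as the expected LC after complete larynx RT, subtracts a margin of 8 points, and states: "if LC in the VC-RT arm is ≥84% at 2-years, we will deem the VC-RT arm acceptable". The next sentence gives the sizing: "With a sample size of 111 patients, over 82% power will detect a margin difference of 8" points, by a one-sided exact binomial test at 0.05. The same section then sets up BOP2 with null hypothesis p_eff < 0.84, alternative 0.92, a Beta(0.84, 0.16) prior, λ = 0.95, exponent 1, and type I error controlled at 0.05.

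The Discussion returns to the figure: "With a target LC of 92% and a margin of 8%, any LC below 84% - therefore below the expected range- would be deemed unacceptable".

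On the comparator, Study design says "The study is powered to compare LC of VC-RT compared to historical outcomes of CL-RT", and gives randomization the purpose of producing control-arm data on secondary and survival outcomes. The Analytic plan says "A Bayesian regression model [63, 64] will be used to compare the LC between the VC-RT and CL-RT arms at 2 years", and the Abstract makes the comparison of LC between the two treatments the primary objective. The Discussion concedes that this is not a true randomized non-inferiority trial.

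**The concern.** A null value and a pass mark are different things. An arm whose observed LC just reaches the null value has not excluded it; to do so, the observed rate must exceed the null by a margin that depends on the sample size. If the sentence on acceptability is applied to the observed result, the 5% error that the same section states does not belong to the rule in use, and a result in the high 80s can be reported as acceptable although the powered test fails.

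The second problem is the comparator. A reader of the Abstract and Analytic plan expects the primary conclusion from VC-RT against CL-RT; a reader of Study design and Statistical considerations expects it from VC-RT against 84%. No passage says which one decides.

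The stakes are high. The Abstract says a positive result would lead to adoption as a standard approach, and the Discussion notes that salvage after local recurrence is frequently total laryngectomy.

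**Working it through.** **Inputs (Statistical considerations).** Evaluable n = 111 in VC-RT; null p0 = 0.84; alternative p1 = 0.92; one-sided alpha 0.05; prior Beta(0.84, 0.16); BOP2 cut-off λ(n/N)^α = 0.95 × 1 = 0.95 at n = N; 116 VC-RT and 39 CL-RT patients randomized, 5% attrition. F is the number of local failures, treated as binomial.

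**1. The stated power reproduces.** The largest f with P(F ≤ f | 111, 0.16) ≤ 0.05 is 11:
- P(F ≤ 11 | 111, 0.16) = 0.0464; P(F ≤ 12 | 111, 0.16) = 0.0818.
- Power: P(F ≤ 11 | 111, 0.08) = 0.823, which matches the stated figure of over 82%.

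The powered test therefore passes at 100/111 = 90.1% or more.

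**2. BOP2 at n = N = 111.** With F failures the posterior is Beta(0.84 + 111 − F, 0.16 + F). Pr(p ≥ 0.84) is 0.973 at F = 11 and 0.949 at F = 12. Against 0.95 the limit is again 11 failures, so the exact test and BOP2 agree at this n.

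**3. The sentence read as a rule on the observed rate.** 94/111 = 84.7% passes and 93/111 = 83.8% does not, so up to 17 failures are accepted.

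| True LC | Sentence accepts (F ≤ 17) | Exact test accepts (F ≤ 11) | Opposite verdicts (F = 12 to 17) |
|---|---|---|---|
| 80% | 13.1% | 0.3% | 12.7% |
| 82% | 27.6% | 1.3% | 26.2% |
| 83% | 37.4% | 2.6% | 34.9% |
| 84% | 48.5% | 4.6% | 43.9% |
| 86% | 71.2% | 13.2% | 58.0% |
| 88% | 88.6% | 30.7% | 57.9% |
| 92% | 99.7% | 82.3% | 17.4% |

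The disputed results are observed LC from 84.7% (94/111) to 89.2% (99/111). Adding the stated interim stop (more than 10 of 55, treated as the same binary endpoint) lowers the 48.5% only to 45.8%.

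**4. Other evaluable numbers.** If fewer than 5% are lost, n lies between 111 and 116.

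| n | Exact test: failures allowed | Exact type I error | Power at 92% | Posterior ≥ 0.95: failures allowed | Type I error |
|---|---|---|---|---|---|
| 111 | 11 | 4.6% | 82.3% | 11 | 4.6% |
| 112 | 11 | 4.3% | 81.5% | 12 | 7.6% |
| 114 | 11 | 3.6% | 79.9% | 12 | 6.6% |
| 116 | 11 | 3.1% | 78.3% | 12 | 5.7% |

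The 0.95 posterior cut-off thus exceeds 5% at n = 112 to 116 (before any interim stop), while the exact test stays within it.

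**5. The between-arm comparison.** Assume 37 evaluable controls (39 × 0.95 ≈ 37), true LC of 92% in both arms and an 8-point margin. The standard error is √[0.92 × 0.08 × (1/111 + 1/37)] = 0.0515, so a 95% interval is about ±10 points. Power at one-sided 5% is Φ(0.08/0.0515 − 1.645) = 46%. A simulated Bayesian version (independent Beta(0.84, 0.16) priors, posterior threshold 0.95) gave about 54%. The margin, priors and threshold for this comparison are assumptions; the article states none.

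**The case against.** Several points against the concern carry weight.

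- **The sentence may name the true rate.** It opens with the margin, the test follows at once, and BOP2 treats 0.84 as a parameter. Read so, it only defines the acceptable region and the 5% stands. This reading is possible. But a decision that follows from the arm's LC at 2 years reads more naturally as applying to the result, and a true rate cannot trigger a decision. The two readings give opposite verdicts on plausible data, so the wording still needs fixing.
- **The Discussion gives only a fail condition.** This stands. "any LC below 84% - therefore below the expected range- would be deemed unacceptable" does not say that 84% or more passes, and an observed LC below 84% also fails the exact test. It does not contradict the test; it only leaves the role of 84% unclear.
- **There are not three incompatible rules.** A reader might count the exact test, BOP2 and the regression as rivals. The documents do not support that: the first two coincide at n = 111, and the regression states no success criterion, so it is a competing comparison and not a rule. Its missing threshold may lie in the full protocol or analysis plan and is not held against the article.
- **The limits of the randomized comparison are disclosed.** This also stands, in Study design and the Discussion. It makes the Abstract's primary objective and the Analytic plan's final comparison harder to reconcile with the rest, not easier.

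**Conclusion.** The concern holds in this form: one acceptance sentence conflicts with the powered test when applied to the observed rate, and the primary objective and final analysis name a different comparator from the one used for sizing. At n = 111 the gap is 17 against 11 permitted failures, or 84.7% against 90.1% observed LC. Opposite verdicts have probability 44% at true LC 84%, 58% at 86% or 88%, and 17% at 92%.

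A reader might infer that the plan would accept an unacceptable treatment about half the time. That is too strong. The 48.5% applies at the 84% boundary, where the 5% error is set; it falls to 37% at 83%, 28% at 82% and 13% at 80%. It also depends on reading the sentence as a rule on the observed rate.

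The figures assume a fully observed binary outcome at 2 years. The Analytic plan also estimates LC by Kaplan-Meier and competing-risk methods; with censoring the counts would shift, but the difference between a null value and a pass mark would remain.

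**What to change.** 1. Replace the acceptance sentence in Statistical considerations by one primary rule: VC-RT is acceptable only if the one-sided exact binomial test rejects LC ≤ 84% at 0.05, at the actual number of evaluable VC-RT patients. That is at most 11 failures for any n from 111 to 116.
2. If the BOP2 posterior rule is to be the final rule instead, recalibrate its cut-off to the actual n, because 0.95 gives a type I error of 5.7% to 7.6% at n = 112 to 116 before any interim stop.
3. State in Statistical considerations and in the Discussion that 84% is the null value and not the pass mark.
4. In the Analytic plan, label the between-arm Bayesian regression of LC a secondary estimate, reported with its 95% credible interval and no non-inferiority claim. Align the primary objective in the Abstract with this.

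The cost is wording; no extra patients or data are needed. The visible pass mark rises from 84% to about 90% observed. Because the exact test is discrete, power at 92% is 82.3% at n = 111 and 78.3% at n = 116.
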